## Abstract

(1) Respiratory syncytial virus (RSV) infection in infants not only affects the child itself, but also their families. Nevertheless, information on the overall impact is scarce. A comprehensive caregiver-specific approach covering essential (health) dimensions and relevant stakeholders was initiated under the ResQ Family study conducted in Germany, France, Italy and Sweden. The primary objective is to investigate the health-related quality of life of parents and/or caregivers of children (<24 months) hospitalised for RSV. (2) Each participant completes an online questionnaire disseminated via social media and printed material in hospitals. Using the PedsQL^TM^ FIM as well as further self-designed questions, parent and patient characteristics as well as potential stressors and preventive factors are recorded at baseline and after six weeks. Multivariate regression models with health-related quality of life as main outcome parameter will be conducted. (3) The study is currently in the recruitment process. A full analysis will be performed once the data collection phase is complete. First results are to be expected in late 2023. (4) Publishing the results in the form of scientific papers but also non-scientific (information) material will help us raise awareness for RSV and the importance of prevention among healthcare professionals, patient representatives and decision-makers.

## 1. Introduction

Respiratory syncytial virus, or RSV, is a highly contagious virus causing lower respiratory tract infections (LRTI), particularly in very young children [1]. It commonly arises during the coldest months of the year; however, shifts were reported due to preventive measures related to the ongoing COVID-19 pandemic [2,3,4]. Each year, on a global scale, RSV leads to approximately 33 million cases of acute LRTI, resulting in more than three million hospitalisations in children under 5 years of age [5]. In the context of a European community setting, direct costs per admission can be estimated at EUR 9682.8 representing a high (socio)economic burden not only for healthcare payers (EUR 4587.9) but also from a societal perspective (EUR 5094.9) [6]. Although preterm infants and children with pre-existing comorbidities are at high risk for acquisition, nearly all infants will have been infected with RSV at least once by the age of two years, resulting in the hospitalisation of one in every 56 healthy term-born infants in high-income countries [1,7,8,9,10]. In the course of the infection, RSV often leads to bronchiolitis and pneumonia requiring (invasive) supportive care measures such as supplemental oxygen, fluid replacement, mechanical ventilation or intubation which might result in long-term complications, such as wheezing or impaired lung function later in childhood [11,12,13].

When the RSV infection takes a severe course, it might not only affect the infant’s health but also significantly impact the life of other family members. Illness and hospitalisation of children are often critical events leading to broad implications on everyday life resulting in feelings of stress and anxiety especially for the affected parents [14]. These conditions are part of the health-related quality of life (HRQoL) concept, a key health outcome indicator in research studies [15,16]. HRQoL is the subjective well-being or quality of life relative to one’s health or disease status and can be conceived as a multi-dimensional approach including emotions, mental health as well as problems in relation to daily activities, work productivity (loss) and family functioning [17,18,19]. In the context of RSV, various stressors associated with the child’s hospitalisation can, therefore, impose a significant burden on the entire family, leading to a wide range of detrimental effects on their daily life [20,21].

To date, previous studies investigated only isolated aspects of paediatric RSV infection in relation to the child’s and/or parental (health-)related quality of life, addressed respiratory diseases in general or did not use a caregiver-specific instrument [21,22,23,24]. However, some studies exploring aspects of the burden of respiratory infections in families were conducted. In 2021, Díez-Gandía and colleagues reported a mean HRQoL loss in a Spanish population of RSV-infected children and their parents of 38% during the first week of symptoms, using an ad hoc questionnaire over a period of 30 days [22]. In France, Lapillonne et al. showed that, in particular, the emotional, physical and daily organisational aspects of all family members were clearly impacted due to the infant’s hospitalisation for bronchiolitis [20,23]. Another study conducted in Sydney, Australia, evaluated an assessment tool to measure the quality of life of caregivers of children with influenza-like illnesses (Care-ILI-QoL) and showed significant decreased total QoL scores in parents with perceived very/extremely sick children [24]. Yet, the impact is not fully known, as there is, to our knowledge, no study available addressing the burden and impact on the entire family, often described as the “Greater Patient” with a caregiver-specific multi-national approach covering essential (health) dimensions and involving relevant stakeholders [25]. To fill existing knowledge gaps, address the public health burden and emphasize the caregiver perspective in this specific field of research, the ResQ Family study (ResQ Family: Impact of Respiratory Syncytial Virus hospitalisation on Quality of life of Families—a multi-country study) was initiated.

This study protocol provides the scientific basis for the ResQ Family project (http://www.resq-family.org, accessed on 10 March 2023). It defines the study design and study objectives, describes the recruitment of the study population and explains the procedures, evaluations and statistical analysis to be performed. The overarching aim of the ResQ Family study is to comprehensively investigate the HRQoL of parents and caregivers of children hospitalised due to RSV by applying a participatory research approach.

The following main hypotheses can be defined:
(a)An RSV infection with hospitalisation has an impact on the health-related quality of life (HRQoL) of affected parents and caregivers;(b)The severity of an RSV infection with hospitalisation is associated with health-related quality of life (HRQoL) of parents and caregivers (over time);(c)Socio-economic status, parental health literacy and support modify the association between the severity of an RSV infection with hospitalisation and health-related quality of life (HRQoL) of parents and caregivers.

## 2. Materials and Methods

### 2.1. Study Population and Design

The ResQ Family study runs from December 2021 until June 2024. Data are collected between September 2022 and May 2023, corresponding to a typical RSV season duration in countries of the northern hemisphere. The project was designed as a multi-country observational study in which parents and caregivers of children hospitalised for RSV were invited to share their experiences via an online questionnaire.

Ensuring geographical distribution across Europe (Northern, Central and Southern Europe), participants living in Germany, France, Italy and Sweden are enrolled in the study. All parents and caregivers whose children (i) are under 24 months of age, (ii) were diagnosed with RSV either by a confirmed test (e.g., ELISA/IFT/PCR from nasal secretion, sputum or throat swab) or a doctor’s diagnosis based on typical symptoms during the RSV season, (iii) were hospitalised no more than four weeks ago (calculated from the day of hospital admission to the day the questionnaire was completed) for at least 12 h due to the respective RSV infection are included in the study.

After completion of the baseline survey, study participants have the opportunity to either end with an anonymous one-time attendance or provide their e-mail address for follow-up participation six weeks later, examining the lasting impact (on the family) after (the child’s) hospitalisation due to RSV.

### 2.2. Participation and Involvement of Relevant Stakeholders

In general, and to ensure the involvement of relevant stakeholders, the ResQ Family project is accompanied by a multi- and transdisciplinary working group comprising the “External Scientific Advisory Board (ESAB)” composed of researchers specialised in the field of respiratory infectious diseases and/or quality of life and further parent and patient representatives as well as healthcare professionals as part of the “Project Expert Group (PEG)”. Each country is, thereby, represented by at least one parent (either as a representative of a national parents’ organisation or an affected caregiver) and one paediatrician or neonatologist experienced with RSV.

Initial ideas for the study design were developed interactively together with all members of the ESAB and PEG during a roundtable discussion in April 2022 and further refined in separate expert and parent meetings. In the following and through regular exchanges, the working group agreed on inclusion and exclusion criteria, gradually developed the questionnaire and generated recruitment materials.

Throughout the recruitment phase, continuous contact will be maintained to review and, if necessary, adapt the recruitment strategy.

### 2.3. Recruitment of Study Participants

Parents and caregivers can be approached during hospital stay, at or shortly after discharge of their child hospitalised for RSV. However, conducting the survey has to take place within four weeks following the first day the child was hospitalised. This time frame was defined taking into account the average length of stay of RSV-infected children in Europe (~2.7 days) as well as the underlying study conditions intending to ensure the recruitment of a maximum number of participants, while avoiding potential recall bias [26].

Participants are mainly recruited by receiving the link to the online survey via social media and newsletter channels of the European Foundation for the Care of Newborn Infants (EFCNI) and their network. In addition, parent organisations, healthcare professionals in hospitals, professional healthcare societies—especially those included in the ESAB and PEG—as well as further networks in Germany, France, Italy and Sweden are encouraged to support the promotion of the study. They are asked to either directly engage in in-person recruitment of possible participants by distributing study-specific printout materials to affected families or to spread the survey online via their network(s).

For this purpose, a multilingual recruitment toolkit was prepared and professionally designed. The toolkit provides an overview of the project communication and survey recruitment strategies in general and includes ready-to-use elements such as graphics and text templates for social media (Facebook, LinkedIn, Instagram, Twitter), mailings, and newsletter communication, as well as templates for printout materials (postcard, flyer/leaflet). To ensure suitability and comprehensibility for the target group, all recruitment and information material was developed and, subsequently, translated in collaboration with a skilled communications team as well as native-speaking parents and medical experts of all four participating countries.

To clarify open questions, to explain the application of the toolkit in more detail and to elucidate the possibility of distributing printout materials, additional briefing calls with experts (ESAB and PEG members) of every participating country were carried out. The toolkit was then made available in all language versions on EFCNI’s project-related website (http://www.resq-family.org, accessed on 10 March 2023) and distributed via e-mail to the expert network developed and involved in the study. In addition, printed postcards were sent to all interested parties who offered to distribute them to affected families in neonatal/paediatric wards in hospitals (e.g., together with the discharge letter) or corresponding networks.

### 2.4. Data Collection

Data for the baseline survey were collected via a self-report online questionnaire of 84 single- and multiple-choice closed questions and one open question. Besides socio-demographics of the participating parent or caregiver and the RSV-infected child, details of the child’s comorbidities as well as the child’s symptoms during RSV infection and hospitalisation are recorded. To assess the impact of the disease on HRQoL of affected families the standardised and caregiver-specific instrument PedsQL^TM^ Family Impact Module (PedsQL^TM^ FIM) as well as further self-designed questions based on existing instruments and literature in the respective field are used [27,28]. Completing the questionnaire requires approximately 20 min in total.

To evaluate changes over time, parents and caregivers who consented for future contact were invited by e-mail to take part in a follow-up six weeks after the baseline survey. A re-query of the PedsQL^TM^ FIM, further single- and multiple-choice closed questions and one open question give participants the opportunity to add more information about persistent symptoms or recovery, possible barriers and the long-term impact of the child’s RSV infection on the family in general. The time required to answer the total of 23 questions in the follow-up survey is estimated at 5–10 min.

All questions of the baseline and follow-up survey were initially set up in English, serving as a master version for the respective country languages. With the help of native speaking parent representatives and health care professionals of the PEG, questions which were not already part of the validated PedsQL^TM^ FIM were then translated into German, French, Italian and Swedish, ascertaining (linguistic) comprehensibility and accessibility to all study participants. To guarantee the expertise of both parents and doctors, each language was reviewed by at least one parent representative and one medical expert fluent in the corresponding language. By using a translation editor, all final language versions were incorporated into SurveyMonkey, an online survey tool which fulfils the requirements of the General Data Protection Regulation (GDPR) [29,30]. After the final set-up, native speakers pre-tested the questionnaire in all four languages.

### 2.5. Research Outcomes and Instruments

#### 2.5.1. Socio-Demographic Characteristics and Child’s Health Status

At baseline, different variables such as age, gender, highest level of education, civil status, (legal) relationship to the child, place of residence and living conditions are included. The presence of a history of prematurity, allergic diseases or other comorbidities as well as symptoms of the current RSV infection and the specific infant’s quality of life are measured using self-developed items adapted from questions by Díez-Gandía et al. [22]. Moreover, a severity index comprising the child’s RSV symptoms based on Leidy et al. will be calculated [21].

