## Figures and Tables

**Table 1 ijerph-20-05917-t001:** Overview on domains/variables/instruments/time points

**Domains**	**Variables/Constructs**	**Score/Instrument and Data Source**	**Time Point**
Parental/family socio-demographic characteristics	Age, gender, highest level of education, civil status, (legal) relationship to the child		t0
Infants’ socio-demographic and health characteristics	Age, gender, place of residence, living conditions and circumstances, gestational age, birth weight, type of pregnancy, nutrition (before and during hospitalisation), history of allergic diseases, compliance with vaccination recommendations, RSV prophylaxis		t0
Infant’s comorbidities	Pre-existing health conditions		t0
Infant’s symptoms during RSV infection and hospitalisation	Place of first diagnosis, type of diagnosis (confirmed diagnosis vs. doctor’s diagnosis), symptoms during or after the RSV infection and hospitalisation, length of hospital stay, type and duration of symptoms, clinical manifestations, supportive care measures, place of treatment	Based on Díez-Gandía et al. [22]	t0, t1
Infant’s quality of life	General behaviour, sleeping behaviour, irritability, playing behaviour, exhaustion, attentiveness, demand for comfort	Based on Díez-Gandía et al. [22]	t0, t1
Worry/concern about child’s RSV infection/symptoms	Degree of overall worry, degree of worry about specific symptoms, feelings about child’s health status during hospitalisation	Based on Díez-Gandía et al. [22]	t0, t1
Presence with the child receiving special/intensive care	Permitted visits and visitors, frequency and duration of visits/presence, interaction with the child, involvement in child’s treatment	Based on Kostenzer et al. [38,39]	t0
Impact of child’s disease on parents/caregiver/family	Physical Functioning	PedsQL^TM^ Family Impact Module [27]	t0, t1
	Emotional Functioning		
	Social Functioning		
	Cognitive Functioning		
	Communication		
	Worry		
	Family daily activities		
	Family relationships		
Parent/caregiver general health status	Scale 1 (very bad)—10 (excellent)		t0, t1
Loss of work productivity	Current professional status, working hours, missed working hours, impact on job productivity, impact on leisure activities		t0, t1
Barriers visiting hospitalised child	Distance, time, additional costs		t0

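### At baseline, the severity index and the HRQoL score come from the same parent in the same questionnaire, so shared-reporter error could produce or inflate the association in hypothesis (b)

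*Protocol article*

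**What the plan says.** Hypothesis (b), at the end of Section 1, states: "The severity of an RSV infection with hospitalisation is associated with health-related quality of life (HRQoL) of parents and caregivers (over time"). Hypothesis (c) asks whether socio-economic status, health literacy and support modify that same association.

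The only severity measure that the article names is in Section 2.5.1: "a severity index comprising the child’s RSV symptoms", based on a cited earlier study. The same section says that symptoms of the current infection, along with other items, "are measured using self-developed items adapted from questions by" a second cited study. The items of the index are not listed.

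Section 2.4 gives the data source: "Data for the baseline survey were collected via a self-report online questionnaire of 84 single- and multiple-choice closed questions and one open question". In it, "the child’s symptoms during RSV infection and hospitalisation are recorded", and the PedsQL FIM is part of the same questionnaire. On duration: "Completing the questionnaire requires approximately 20 min in total". Section 2.5.2 makes the FIM the main parent-reported outcome, at baseline and at follow-up; its dimensions include emotional functioning and worry.

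Section 2.6 plans correlations between caregiver quality of life and severity, then regression models. The example confounders are socio-economic factors, RSV prophylaxis, comorbidities, prematurity and symptom status.

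Table 1, in the domain for the infant's symptoms, also lists "length of hospital stay, type and duration of symptoms, clinical manifestations, supportive care measures, place of treatment".

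**The concern.** Hypothesis (b) is worded as a statement about the infection. As described, its baseline test compares two reports by one person at one time. A parent who is distressed when answering may report more or worse symptoms in the child and also poorer functioning of their own. Exposure and outcome then share an error source, and a correlation can appear even if clinical severity and caregiver HRQoL are unrelated.

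The Introduction itself cites a study with a related pattern: "significant decreased total QoL scores in parents with perceived very/extremely sick children". That study concerned influenza-like illness and used a different instrument, so it does not show that the bias is present here. It does show why perceived and clinical severity need to be kept apart.

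At stake is how a positive result can be read. Without a second measure of severity, it cannot be told whether families of sicker children fare worse or whether more distressed parents report sicker children. A modifier analysis under (c) inherits the same ambiguity, and the findings are meant for policy makers (Section 2.7).

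**Working it through.** The article gives no sample size, effect size or power, so there is no planned figure to reproduce. The check has two parts.

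**1. Source of exposure and outcome**

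| | Content | Respondent | Time |
|---|---|---|---|
| Severity index | Child's RSV symptoms (2.5.1) | Parent or caregiver (2.4) | Baseline survey; symptoms asked again at t1 (Table 1) |
| PedsQL FIM | Caregiver and family functioning (2.5.2) | Parent or caregiver | Baseline survey; repeated six weeks later |

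The article describes no chart, clinician or laboratory source for severity. None of the example confounders in Section 2.6 measures parental distress or reporting style. Symptom status is on that list, but it overlaps with a symptom-based exposure and cannot remove the shared error.

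**2. How large the effect could be**

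Every input here is an assumption except the 5% level (Section 2.6), which is taken as two-sided. Set the true severity–HRQoL association to zero. Let distress correlate +a with the reported symptom index and −b with the FIM. Then:

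- induced correlation: r = −a × b
- Fisher z: d = atanh(|r|) × √(N − 3)
- rejection probability: 1 − Φ(1.96 − d) + Φ(−1.96 − d)

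Worked case, a = b = 0.3 and N = 200: |r| = 0.09, atanh(0.09) = 0.0902, √197 = 14.04, d = 1.27. The rejection probability is 24%.

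| a = b | r | N = 200 | N = 400 |
|---|---|---|---|
| 0.2 | −0.04 | 9% | 13% |
| 0.3 | −0.09 | 24% | 44% |
| 0.4 | −0.16 | 62% | 90% |
| 0.5 | −0.25 | 95% | >99% |

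The nominal rate is 5%. If the symptom loading is weak and the FIM loading is not (a = 0.1, b = 0.5), r = −0.05 and the rate at N = 200 is 11%. For any fixed non-zero r the rate rises with N, so better recruitment does not cure the problem.

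**Over-time analysis.** If baseline severity is related to the six-week FIM, the sitting differs, and the induced correlation becomes −a × b × s, where s is the stability of distress over six weeks (also assumed). With a = 0.3 and b = 0.5, simulation with 4,000 runs per setting gave:

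| | N = 200 | N = 400 |
|---|---|---|
| Baseline FIM | about 56% | about 85% |
| Six-week FIM, s = 0.3 | 9% | 15% |
| Six-week FIM, s = 0.5 | 18% | 32% |
| Six-week FIM, s = 0.7 | 32% | 57% |

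The bias weakens but does not vanish while distress persists. Symptoms at t1 set against the FIM at t1 would share a sitting again.

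**The case against.** The strongest objection is that the content of the index is unknown. The article lists no items, and Table 1 places supportive care, length of stay and place of treatment inside the symptoms domain, so the index may already contain some of them. This stands. A reader might infer that the index measures only perceived severity; the document does not establish that.

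It is also not shown that the index uses graded ratings. The questions are closed, and worry about symptoms is recorded as a separate construct. This limits how strong the bias can be presumed to be, but a yes/no symptom item answered from memory is still the parent's report.

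The magnitude is wholly assumed. That stands: the figures show that the bias is possible, not that it is likely or large. Reading the upper end as the expected error rate would be wrong.

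The limitations in Section 4 mention self-report bias and rule out causal claims. This helps only in part. The self-report caveat is generic, with social desirability as its example, and shared-reporter error distorts the association itself, not only its causal reading.

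Finally, one might want to replace the symptom index by treatment events and credit severity only when those show an association. The document does not support going that far. Treatment events are also parent-reported, are coarser and partly reflect practice in four countries. Parents may answer during the stay (Section 2.3), so length of stay can be incomplete. Intensive care and a long stay may also affect parents by other routes, such as visiting limits and missed work. These points argue for a second analysis alongside the index, not for a replacement.

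**Conclusion.** The point holds as a limit on interpretation. At baseline, hypothesis (b) relates a parent-reported, symptom-based index to an HRQoL score from the same parent in the same questionnaire, and the article neither names nor handles the shared error. Hypothesis (c) uses the same exposure.

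The size is not known. Under the assumed equal loadings of 0.2 to 0.5, no true association and N = 200, the false-association rate runs from about 9% to 95%. Relating baseline severity to the six-week FIM lowers it. If the index already includes treatment events, the bias would be smaller.

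The document does not show that the planned association is spurious or that the index is unusable. It shows that a positive baseline result, taken alone, could not separate clinical from perceived severity. A cheap improvement is worth making.

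**What to change.** - Keep the symptom index, and list its items so that any treatment events in it are visible.
- Pre-specify, for (b) and (c), a parallel analysis with a severity measure built only from the treatment-event items already in Table 1: supportive care measures, place of treatment and length of stay. Adjust it for country, and treat length of stay as incomplete for children still in hospital at the survey.
- Report both exposures side by side, and also show baseline severity against the follow-up FIM.
- Describe an association seen only with the symptom index as one with parent-perceived severity.
- Name shared-reporter bias among the limitations in Section 4.

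The cost is analysis-plan wording and one additional set of models, with no new data. The downside is that the treatment-event measure is coarser, is still parent-reported and partly reflects between-country practice. Agreement between the two exposures would therefore strengthen the reading of (b) without proving it.
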